#### Qualitative data

Qualitative data from interviews with families will be transcribed and analyzed using grounded theory, a qualitative approach that is used to analyze social processes present within human interactions [38]. Application of the theory can result in explanations of important family processes or structures that are grounded in the empirical data. Major themes can be inductively derived from the data to articulate the dynamics of psychosocial family environment.

### Statistical power and sample size

When this study was originally conceptualized in 2003, few data were available in the literature describing the variability in insulin resistance, assessed using fasting HOMA-IR, among overweight African American children. Thus, since it was expected that the qualifying children would be hyperinsulinemic but not hyperglycemic, sample size was estimated using values for plasma insulin. For evaluation of the effectiveness of the intervention, a sample of 50 children in the intervention group and another 50 in the control group was determined to allow detection of a difference in plasma insulin levels of 4 μU/ml, assuming an initial fasting plasma insulin of 30 μU/ml [39-41], a standard deviation of 7.2 μU/ml [42] and a correlation coefficient of 0.6 between initial and final values in the control group (Type I error = 0.05, and Type II error = 0.20). A total sample size of 150 participants at baseline (75 per group) was initially planned for, based on an estimated yearly attrition rate of 33%. Because the attrition rate was higher than anticipated following the first year of Wave 1, the number of participants was increased during the course of this study.

### Training

#### Control staff

YMCA staff at the control site received the in-house YMCA training provided to all new staff, and a limited 1-hr orientation to the project.

#### Intervention staff

Implementers of the TAT intervention included UC Berkeley staff and students, and YMCA staff. The adult-to-child ratio was 1:8 for most intervention activities. Site instructors and key YMCA staff received in-house YMCA training, plus program-specific training prior to commencement of each program year, followed by weekly and monthly training (referred to hereafter as "initial" and "continuing" training, respectively). Initial training aimed to provide an understanding of expectations with respect to participant confidentiality, safety and communications; the nature of each curriculum component; and the influence of self esteem and of eating and physical activity behaviors on risk of T2DM. Continuing training focused on team building (3 hr/yr), health lifestyle challenges in an obesigenic environment (3 hr/yr), managing challenging behaviors in children (8 hr/yr), use of social cognitive theory in practice (2 hr/yr), nutrition lesson-specific training (40 hr/yr), physical activity lesson-specific training (10 hr/yr), self-esteem lesson-specific training (10 hr/yr), and strategies for motivating families (Table 6).

**Table 6 T6:** Training Components and Content

Program Component	Training time	Content
1. Introductions, team-building, project overview^1^	1 hr during initial and yearly training (+3 hr additional during year-long program)	Introduce personnel roles. Describe the research project and program. Build team atmosphere. Introduce Body Positive and Health at Every Size concepts.
2. Healthy lifestyle challenges in an obesogenic environment^2^	1 hr (+0 hr)	Introduce nutrition, physical activity and self-esteem goals. Discuss challenges African American families experience in inner-city Oakland in efforts to live a healthy lifestyle.
3. Managing challenging behaviors in children^2^	1 hr (+8 hr)	Introduce positive behavioral management approaches and describe how to effectively develop social skills and problem-solving abilities in children.
4. Social cognitive theory (SCT) in practice^2^	1 hr (+2 hr)	Understanding and using self-observation, peer modeling, feedback, verbal encouragement, mastery through trials of increasing difficulty.
5. Nutrition^2^ General Lesson-by-lesson	1 hr (+2 hr) 0 hr (+40 hr)	Describe components of healthy diet, considerations of African American culture, income, food availability and transportation; demonstrate use of SCT3, importance of fun.
6. Physical activity^2^ General Lesson-by-lesson	1 hr (+2 hr) 0 hr (+10 hr)	Discuss barriers, use of Health at Every Size concept and SCT to increase activity self-efficacy, motivational strategies, cultural preferences and considerations.
7. Self-esteem^2^ General Lesson-by-lesson	1 hr (+2 hr) 0 hr (+10 hr)	Describe contributors to and effect of positive self-esteem, cultural differences in expression. Discuss strategies to develop self-esteem using Body Positive approach, preventing harm.
8. Motivating families^2^	1 hr (+1 hr)	Influence of parenting style, family food and activity practices, and community environment on development of healthy behaviors; motivational strategies; cultural considerations.

^1 ^Separate sessions for Control and Intervention site staff.

^2 ^Intervention site staff only.

### Intervention curricula and delivery to children

Each program year began with a kick off to integrate all elements of the curricula in a fun-filled, action-packed 2 weeks of YMCA day-camp. Children were provided ample opportunities to bond with each other and staff to promote continued participation. A celebratory family event was held at the end of the 2 weeks for children to showcase the program to their families.

Yearly schedule of child activities included 10 days (8 hr per day) of program-specific summer day-camp, plus 1 (2-hr) session/wk, 3 weeks per month, 11.5 month for a total of 150 hr (50% devoted to physical activity and 25% devoted each to nutrition and self-esteem building) for children.

With goals and a theoretical model for *TAT *as a guide, we examined relevant curricula from peer-reviewed scientific literature and on-line sources. Materials were evaluated for: age-appropriateness; socio-cultural relevance; body weight neutral (incorporating a 'health at every size' approach); current within 10 years; experiential (a hands-on, rather than didactic, approach to learning); and resonance with program goals. No single program curriculum was identified that met all project criteria. Thus, select materials were used from a variety of curricula and, as needed, adapted for use with our target population.

#### Educational components

Lessons and activities focused on improvements in dietary quality and quantity, increased time in moderate-to-vigorous activity, and healthy self-esteem building through strengthening of cultural pride and social and behavioral competence. Conceptual elements included knowledge and skill building, modeling, goal setting, self-assessment, practice and reinforcement. Educational strategies included individual practice, cooperative learning, and individual and group discussions. Modules (6 modules, 5 weeks each), and lessons within modules, were sequenced to equip children with knowledge, skills, self efficacy and intentions to make healthy diet and physical activity choices. Examples of lessons delivered in this program are available online http://www.cnr.berkeley.edu/cwh/.

#### Nutrition component

The core nutrition lessons utilized the approach of "The Power of Choice: Helping Youth Make Healthy Eating and Fitness Decisions" [43], and included 'hands-on" learning via preparation of low-cost, culturally appropriate foods, taste testing, and exposure to new foods and ingredients. Lessons were conducted with a minimum of equipment in modest facilities, and aimed to develop knowledge, challenge children to identify healthy options and make healthier food choices within usual settings of fast food outlets and corner stores, set personal goals, and self-assess in order to refine goals. Nutrition topics were sequenced as follows: making low fat choices, increasing fruit and vegetables, replacing sugar and portion size, replacing refined with whole grains, healthy snacks and hunger cues, moderation and a balanced diet.

#### Self-esteem component

Core self-esteem lessons were developed based on the widely-used curricula, Body Positive [44], a program designed to promote health at every size, body satisfaction and self-esteem, and Kwanza-based activities designed to promote cultural pride and build community. As needs became evident, health and behavior lessons were adapted from the approach of Kids' Health [45] to address topics such as hygiene, acne, puberty, anger management, bullying, and being teased. Self-esteem topics were sequenced as follows: self awareness & cultural expression of self, positive interaction, effective communication, Body Positive, 'Health At Every Size' & respect of self and others, taking charge of your personal hygiene, overcoming challenges (including bullying, teasing and conflict), self-assessment of personal challenges, and positive growth.

#### Physical activity component

Activities were designed to consider the body weight and fitness status of children, with gradual and manageable increases in difficulty, duration and frequency. Activities, based on the After-School SPARK [46] physical activity program, were child-centered, encouraged enthusiasm and participation, and aimed to increase enjoyment through games, dance and sports. Physical activity programming was sequenced as follows: flexibility, strengthening, endurance, balance and coordination, speed and agility. Children were encouraged to be active daily even when family members or peers were not, including outside of *TAT *program time; for this purpose all children received a free YMCA membership, allowing access to the facility. Although we acquired evidence that children used these free memberships to utilize the YMCA facilities, their effectiveness at increasing the overall activity of children outside of program could not be selectively determined within the design of this study.

### Parent programming

Studies of obesity prevention have shown that parental involvement is critical to substantively alter children's dietary intakes and energy expenditures [47]. For adult family members, monthly mailing of health education materials, educational meetings (including advertisements about other free, family-focused healthy lifestyle events available in the community that supported TAT goals), phone calls, and/or in-home visits to target overcoming barriers to adopting healthy behaviors, were scheduled. Also 3 healthy lifestyle events and family celebrations were scheduled for intervention group children and families. At the completion of year-end evaluations and data collection, a celebratory family event honored and acknowledged the gains of the child participants.

Parents/guardians were invited also to nine 1-2 hr sessions each year. The curriculum for adult family members in the intervention group relied on the interactive (discussion, information, and food & physical activity demonstrations) "Eating Smart. Being Active" adult EFNEP lessons regarding the importance of physical activity; meal planning, food shopping, reading food labels; increasing intakes of vegetables, fruit, whole grains and calcium-rich foods; portion control; and approaches to limiting intakes of fat, sugar and salt http://efnep.ucdavis.edu/AdultCurriculum.html.

### Outcome and process evaluation

Data collection (Table 1) was designed to allow the effects of intervention to be determined on the primary outcome variable (insulin resistance) and on intermediate outcomes (dietary intakes, physical activity). Changes in behaviors (self efficacy, self esteem) expected to precede changes in primary and intermediate outcomes also were assessed. Finally, collection of data for potential modifiers facilitated increased statistical power by their inclusion, if indicated, as covariates. Outcome evaluations were performed at baseline, and after one and two years of intervention. To maximize objectivity, evaluation staff were different from intervention staff. Process evaluation data were collected to assess the quantity and quality of program services delivered, and responses of child participants, adult participants, paid staff and volunteers (Table 7).

**Table 7 T7:** Process Evaluation Data Collection in *Taking Action Together*

Variables	Methods and Frequency^1^
Adherence to schedule of lessons	Observation - monthly for child component; twice per year for adult component Log - recorded weekly; reviewed monthly
Fidelity of lesson delivery	Observation - monthly for child component; twice yearly for adult component Session evaluation forms - recorded weekly, reviewed monthly
Training, support and monitoring of staff	Observation of attendance and engagement Observation of lesson delivery - bimonthly (child component), twice per year (adult)
Response of participants to sessions	Attendance log - by session; reviewed monthly Session evaluation form - administered lesson-by-lesson (child component), twice per year (adult)
Response of staff and volunteers to sessions	Session evaluation form - administered lesson-by-lesson for child sessions Meeting of staff and volunteers - twice per year
Family response to mailings	Telephone survey - contact intervention families once per year
Overall assessment of program	Confidential telephone survey of intervention families - end of year

## Discussion

### Lessons learned

#### Glucoregulation

Analyses performed to date show that the intervention program stabilized or improved glucoregulation in children after 1 year, the effect being larger in boys than in girls [48]. Also, a larger percentage of children in the treatment group (vs. control) decreased BMI z-scores after 1 yr.

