### Hypotheses and specific aims

Consistent with social cognitive theory, we postulated that development of self efficacy with respect to targeted behaviors would improve children's dietary intake, physical activity, and self esteem which, in turn, would reduce insulin resistance in part by stabilizing body weight. Thus, our main hypothesis was that children in the treatment group would show more favorable changes in insulin resistance than children in the control group following 1 or more 2 years in the program. A secondary hypotheses was that there would be greater improvements in the treatment group in dietary intakes and physical activity. A third hypothesis stated that early markers of behavioral change (dietary and physical activity self efficacy, self esteem, positive behaviors and communications) would be improved in the treatment group when compared to the control.

Thus, the specific aims were (1). To assess the influence of treatment group status on change in insulin resistance (fasting HOMA-IR), (2). To determine the influence of treatment group status on change in intermediate outcomes (diet and physical activity), and (3). To determine the influence of treatment group status on change in potential moderating or mediating variables (self esteem, self efficacy, psychobehavioral characteristics).

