#### Quantitative data

Quantitative data were managed using computer programs including Microsoft Excel, EpiData, BASC-2 software [34], USDA Nutrient Database [35] and MyPyramid Equivalents Database [36]. Data were double entered and edit checks were incorporated into the data entry program to identify data entry errors. For psychosocial, knowledge and attitude measures, scales will be developed as necessary and compared as described above.

Mean changes in the quantitative outcome variables of interest (HOMA-IR and secondary anthropometric, dietary and activity variables) over one or two intervention years will be evaluated using multiple regression techniques. Adjustment for multiple comparisons will not be made, and with values for p < 0.05 considered statistically significant [37]. In addition, because some of these outcome measures are considered to be intermediary or confounding variables, we will use multiple linear regression to examine the effect of intervention on the primary outcome variable of interest (HOMA-IR), adjusting for baseline HOMA-IR, BMI z-score, psychosocial measures such as self esteem, diet and physical activity behaviors, and other potentially relevant factors such as family and (to account for genetic differences in response to intervention) intrauterine history of T2DM. The correlations of all potential covariates with both the dependent and independent variables will be examined, and variables that correlate at p < 0.25 with both variables will be included in the models.

Initially, we will examine the regression coefficient for intervention status (a dummy variable where 1 = intervention group, 0 = control group) in a simple regression model. Using change in HOMA-IR as one dependent variable example, we will model as follows:

Next, we will examine the effects of other explanatory and/or confounding variables to determine whether they explain the effects of intervention status (if any) using as an example:

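### A larger effect in boys is reported, but the described analysis contains no interaction test and uses modifiers only as covariates

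*Protocol article*

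**What the plan says.** All references are to the protocol article.

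- **Discussion, Glucoregulation:** analyses to date are said to show a favourable one-year effect, "the effect being larger in boys than in girls". A separate report is cited. The sentence names no specific measure and gives no estimate, interval or test of the sex difference.
- **Hypotheses and specific aims, aim 3:** the question is the "influence of treatment group status on change in potential moderating or mediating variables".
- **Quantitative data:** in a simple model, "we will examine the regression coefficient for intervention status". After that, "we will examine the effects of other explanatory and/or confounding variables to determine whether they explain the effects of intervention status". Intrauterine history of type 2 diabetes is among the adjustment variables, "to account for genetic differences in response to intervention". The equations that follow the prose are not visible.
- **Reducing bias due to non-randomization:** gender and pubertal stage are covariates to be used if needed. A variable enters when it is related at p < 0.25 to both treatment group and change in the outcome.
- **Outcome and process evaluation:** "collection of data for potential modifiers facilitated increased statistical power by their inclusion, if indicated, as covariates".
- **Statistical power and sample size:** 50 per group for one overall difference in plasma insulin. No subgroup or interaction is sized.

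**The concern.** To say that an effect is larger in boys is to claim effect modification. It needs an estimate of the difference between the two sex-specific treatment effects, with its uncertainty. The described analysis offers only the intervention coefficient, without and then with covariates.

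The gap is more than missing detail, because the document gives modifiers a role that cannot do the job. A covariate entered as a main effect shifts the expected outcome equally in both groups; it does not let the treatment effect vary. Adjusting for intrauterine history therefore cannot capture differing response. The p < 0.25 rule screens for confounding, and a strong modifier that is balanced between groups would fail it. Aim 3 places moderators and mediators under one question, how treatment changes them. That question can inform mediation but not moderation.

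At stake is a sex-specific efficacy statement, in an article that offers its protocol as a model for later programmes, with nothing to show how firm the statement is.

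**Working it through.** **Inputs.** Year-1 completers (Table 3): control 33 boys and 34 girls (67), intervention 28 boys and 41 girls (69). Planning values (Statistical power and sample size): difference 4 μU/ml, SD 7.2, correlation 0.6, alpha 0.05, power 0.80. No SD for change in HOMA-IR is given, so results are in SD units or on the insulin planning values. Tests are taken as two-sided, with 1.960 + 0.842 = 2.80.

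**The plan's own figure.** n = 2 × (7.2 × 2.80 / 4)² ≈ 51 per group, against the stated 50. This uses the unadjusted SD; using the stated correlation gives 41 (change score) or 33 (ANCOVA). Attrition: 50 / 0.67 ≈ 75, as stated. The calculation covers the overall difference only.

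**Standard errors at year 1, in SD units.**
- Main effect: √(1/67 + 1/69) = 0.172.
- Boy-girl difference in effect: √(1/33 + 1/28 + 1/34 + 1/41) = 0.346.
- Ratio: 2.02.
- Detectable at 80% power: 2.80 × 0.346 = 0.97 SD.

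**Power for a boy-girl difference as large as the planned 4 μU/ml**, from Φ(4/SE − 1.96):

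| Residual SD | Main-effect power | Interaction SE | Interaction power | Detectable at 80% |
|---|---|---|---|---|
| 7.20 (post-only) | 0.90 | 2.49 | 0.36 | 7.0 |
| 6.44 (change score, 7.2 × √(2 × 0.4)) | 0.95 | 2.23 | 0.43 | 6.3 |
| 5.76 (ANCOVA, 7.2 × √(1 − 0.36)) | 0.98 | 1.99 | 0.52 | 5.6 |

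With four equal cells the interaction variance is four times that of the main effect. Power of 80% for an interaction of 4 μU/ml would then need about 204, 163 or 131 per arm.

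**Chance that exactly one sex is significant when the true effect is equal.** With power a in boys and b in girls, this is a(1 − b) + b(1 − a).
- 4 μU/ml, post-only: a = 0.58, b = 0.67, giving 0.47.
- 4 μU/ml, change score: a = 0.68, b = 0.76, giving 0.41.
- 4 μU/ml, ANCOVA: a = 0.77, b = 0.85, giving 0.31.
- Assumed common effect of 0.5 SD: a = 0.49, b = 0.58, giving 0.50.

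**Would sex pass the p < 0.25 rule?** At baseline, boys are 51/111 against 52/124: z ≈ 0.62, p ≈ 0.54. Among year-1 completers they are 33/67 against 28/69: z ≈ 1.02, p ≈ 0.31. On either count sex fails the group-association half of the rule, so it would not enter even as a covariate.

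**Year 2.** The Table 3 intervention total is 35, but its split is printed as 17 boys and 28 girls, which sums to 45. The cohort rows give 14 + 4 = 18 girls. With 18, SE = √(1/16 + 1/22 + 1/17 + 1/18) = 0.472, and 2.80 × 0.472 = 1.32 SD is detectable.

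**The case against.** The strongest reply is that the boys statement is a reported result from a cited paper, not a planned analysis, and that paper may contain a proper interaction test. The equations are not visible, and interaction terms are often left to a full protocol or SAP. All of this stands. It limits the point to what this document's prose describes, and it means the sex difference cannot be called unsupported outright. It does not rescue the use of modifiers as covariates, which the document states itself.

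Four stronger readings are tempting and should not be drawn:

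- **That the plan prescribes separate analyses by sex.** It does not. The 31% to 50% range shows the risk of comparing by-sex p-values; it does not describe a planned procedure.
- **That aim 3 leaves a moderation test unanswered.** It asks only how treatment changes the variables, and the described regression fits that question. The fault is that moderators and mediators are not separated.
- **That puberty explains the sex contrast.** Each sex is compared with same-sex controls, so pubertal change common to both arms cancels. A residual imbalance between the two sites within sex cannot be excluded, but nothing shows one.
- **That the article steers users toward boys.** Its abstract, conclusion and expansion proposals mention no sex difference.

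It is also fair to say that adding an interaction now is data-driven, since the result has been seen. That is why it should be labelled exploratory.

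**Conclusion.** The point holds in limited form. The article states a sex difference in effect with no estimate or interval, and its described analysis contains no means of estimating one. It also treats effect modification as a matter of covariate adjustment, which is an error of method.

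The precision available for a sex difference is about half that for the main effect. Year-1 data could detect about 0.97 SD with 80% power, and a boy-girl difference the size of the planned effect would have 36% to 52% power. These figures assume equal variances across cells, two-sided 5% tests, a normal approximation and, for the insulin-scale values, the document's planning figures. The 50% figure further assumes a common effect of 0.5 SD, which the document does not give.

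The primary comparison is unaffected. The change is worth making but is not critical. The Table 3 slip is clerical and does not bear on the one-year statement.

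**What to change.** - **Quantitative data:** add a treatment-by-sex term to the HOMA-IR model adjusted for baseline HOMA-IR. Report the boy-girl difference in effect with its 95% CI and label it exploratory. Treat any other named modifier, including intrauterine history, the same way: a product term with its baseline value, also exploratory.
- **Glucoregulation:** give the estimate and interval, from the cited report if it has them, or state that a sex difference was not established.
- **Hypotheses and specific aims, and Outcome and process evaluation:** separate moderators (treatment effect varies with the baseline value), mediators (changed by treatment) and covariates (adjustment or precision).
- **Table 3:** correct the year-2 intervention split to 17 boys and 18 girls.

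The cost is one extra term per modifier on data already collected, plus text edits. The downside is a wide interval and a weaker statement about boys.
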